12.3.2. Adverse events

Adverse events will be tabulated by treatment arm and type, and Fisher’s exact test will be used to compare AE incidences.

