3.1.4. Contraindications

A history of serious hypersensitivity to the ingredients of TS-1; serious myelosuppression; serious renal dysfunction; serious hepatic dysfunction; current treatment with another fluorinated pyrimidine antineoplastic; current treatment with flucytosine; pregnancy or potential pregnancy

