7.3. Discontinuation of protocol treatment

The protocol treatment will be discontinued if any of the following conditions apply.

1) Confirmed metastasis or relapse of primary disease

2) Confirmed secondary cancer (double cancer)

3) Subject has died.

4) The TS-1 dose is < 80 mg/day or the UFT dose is < 300 mg/day, as a result of applying the dose reduction criteria

5) The rest period exceeds 28 days.

6) The subject withdraws consent for the protocol treatment (TS-1 or UFT treatment).

7) The subject’s ability to keep appointments is compromised by transferring hospitals, etc.

8) The subject is found to be ineligible after enrollment.

9) The (sub)investigator otherwise determines that continuation of the protocol treatment is compromised.

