7.4. Follow-up at discontinuation of protocol treatment

Except for the subjects listed below, every effort will be made to follow-up for survival, metastasis, and relapse all of the subjects who discontinued the protocol treatment, based on the provisions in 7.3. If metastasis or relapse is confirmed, only outcome will be followed up.

1) The subject died.

2) The subject withdrew consent to be followed up.

3) The subject was found to be ineligible after beginning the protocol treatment.

4) Follow-up was compromised for some other reason.

Follow-up after treatment discontinuation will be performed every 3-6 months, counting from the starting day of the protocol treatment.

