# Adverse Event Evaluation and Reporting

8.1. Definition of adverse event

An adverse event (AE) is any undesirable medical event occurring in a subject receiving the protocol treatment. An AE does not necessarily have to show a definite causal relationship with the protocol treatment. Thus, an adverse event is any undesirable or unintended sign (including abnormal clinical laboratory values), symptom, or disease occurring when the protocol treatment is received regardless of the causal relationship to the protocol treatment.

An AE is a serious adverse event (SAE) if it is any of the following.

1. Death

2. Life-threatening

3. Admission to a hospital or clinic or prolongation of admission that is necessary for treatment

4. Disability/incapacity

5. An event that may result in disability/incapacity

6. Any other serious event consistent with 1-5.

7. Congenital diseases or abnormalities in subsequent generations

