12.2. Analysis set

The analysis set will consist of the group of all eligible subjects receiving part or all of the protocol treatment.

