17.2. Early termination of the study

17.2.1. Rules for early termination of the study

The study will be terminated early in the following cases.

1) As a result of evaluating study progress reports from the lead investigator and study monitoring reports, it is concluded that completion of the study is compromised by slow enrollment, frequency of protocol deviations, or the like.

2) Interim analysis confirms the superiority of the test treatment’s efficacy.

3) Interim analysis confirms the inferiority of the test treatment’s efficacy.

4) Adverse events satisfying the following criteria are observed, and it is determined that there are problems with the safety of the protocol treatment.

∙ Protocol-treatment-related deaths 10 subjects

∙ Protocol-treatment-related serious adverse events, including deaths 25 subjects

∙ Protocol-treatment-related Grade 4 neutropenia 25 subjects

5) It is concluded that there are problems with the safety of the protocol treatment as a result of evaluating related information obtained from other studies, scholarly articles, academic conferences, or the like, or it is concluded that continuation of the study is no longer significant.

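### The only analysis set is limited to eligible subjects, so on its natural reading the adverse-event tables and Fisher tests leave out subjects who took TS-1 or UFT and were later found ineligible

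*Protocol*

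**What the plan says.** Protocol section 12.2 defines a single population: "The analysis set will consist of the group of all eligible subjects receiving part or all of the protocol treatment". It is not restricted to efficacy, and no separate safety set is defined.

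Section 12.3.2 follows under the same chapter: "Adverse events will be tabulated by treatment arm and type", with incidences compared by Fisher's exact test. It names no population of its own.

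Two other sections expect some dosed subjects to prove ineligible. Section 7.3 item 8 lists among the reasons for stopping protocol treatment: "The subject is found to be ineligible after enrollment". Section 7.4 item 3 lists among the exceptions to further follow-up: "The subject was found to be ineligible after beginning the protocol treatment".

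The definition in section 8.1 depends on treatment alone: "An adverse event (AE) is any undesirable medical event occurring in a subject receiving the protocol treatment". Section 8.2 has events evaluated during protocol treatment and up to 30 days after its completion, also without an eligibility condition.

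**The concern.** A safety comparison should describe the people who were exposed to the drugs. Here membership of the only analysis set depends on eligibility as well as exposure. A subject who takes TS-1 or UFT, has an adverse event and is later ruled ineligible has that event recorded, yet falls outside the set that is tabulated and tested.

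Adverse events are a named secondary endpoint (Objective; section 11.2.3), and 12.3.2 is the protocol's only planned comparison of toxicity between the two drugs. What is at stake is the completeness of that final comparison. Changing the disease-free survival analysis to all randomized subjects would not by itself settle the matter, because the safety population should follow drug intake.

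**Working it through.** No figure in the protocol bears directly on this point. The check is a comparison of sections, followed by an illustration of size.

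**Sections side by side**

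| Question | Section | Answer |
| --- | --- | --- |
| Who is analysed? | 12.2 | Eligible subjects who received any protocol treatment |
| Is another population named for adverse events? | 12.3.2 | No |
| Can a subject be dosed and then found ineligible? | 7.3 item 8, 7.4 item 3 | Yes, both foresee it |
| Are such a subject's adverse events collected? | 8.1, 8.2 | Yes, on receipt of treatment |
| Is the subject in the adverse-event table? | 12.2 with 12.3.2 | No, on the natural reading |

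**Inputs for size**

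- Subjects per arm: 250 (section 10.1).
- Share f of treated subjects later found ineligible: not given; assumed 2%, 5% or 10%.
- Event rate r in eligible subjects and risk ratio RR of ineligible to eligible subjects: not given; assumed as shown.

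**Subjects left out per arm.** 250 × 0.02 = 5; 250 × 0.05 = 12.5, taken as 12; 250 × 0.10 = 25.

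**Chance that at least one observed case leaves an arm's table.** With k subjects left out, each with event risk p, this is 1 − (1 − p)^k.

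| Event risk p | k = 5 | k = 12 | k = 25 |
| --- | --- | --- | --- |
| 1% | 5% | 11% | 22% |
| 5% | 23% | 46% | 72% |

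**Effect on incidence.** Incidence in all treated subjects is r × [1 + f × (RR − 1)], while the plan reports r. With r = 10%:

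- RR = 1, any f: 10.0% in all treated, 10.0% reported. No bias.
- f = 2%, RR = 2: 0.10 × 1.02 = 10.2%. Understated by 0.2/10.2 = 2%.
- f = 10%, RR = 3: 0.10 × 1.20 = 12.0%. Understated by 2.0/12.0 = 17%.
- f = 10%, RR = 0.5: 0.10 × 0.95 = 9.5%. Overstated by 0.5/9.5 = 5%.

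**Effect on the Fisher test.** Take 25/250 versus 12/250, p = 0.039. Remove five ineligible subjects from the first arm only:

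- none of them with the event: 25/245 versus 12/250, p = 0.026;
- two of them with the event: 23/245 versus 12/250, p = 0.054.

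The omission can therefore move the planned test either way. The counts are invented and one arm is left untouched, so this shows that a change is possible, not that it is likely.

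**The case against.** The strongest reply is that the restriction is inferred. Section 12.3.2 states no population, 12.2 is one generic sentence, section 8.1 defines adverse events over everyone treated, and a safety set is often left to the SAP, which is not at hand. It is fair that the restriction is a reading of the text. But 12.2 speaks of the analysis set in the singular, without qualification, directly before 12.3. An SAP that added a safety set would be departing from the protocol rather than filling a gap in it.

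Several stronger readings are tempting, and the documents do not support them.

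- *The omitted subjects are mainly those with poor organ function, so toxicity is concentrated among them.* The laboratory limits of 5.1 item 10 are recorded on the enrollment form (9.1.1), and the tests are repeated on Day 1 (9.1.2, 9.2). These violations are among the easiest to see before dosing. Late ineligibility could as well concern histology, stage, nodal level or an earlier cancer.
- *The omission favours one drug, because only TS-1 lists* "serious renal dysfunction; serious hepatic dysfunction" *as contraindications (3.1.4).* The UFT list (3.2.4) has serious diarrhea and serious complicating infections, which the TS-1 list lacks. Both include serious myelosuppression, and one set of eligibility criteria applies to both arms. No direction follows.
- *Fatal or severe events could disappear from the trial.* Serious-event reports go to the independent data monitoring committee (section 13), and the stopping counts of 17.2.1, such as "Protocol-treatment-related deaths 10 subjects", carry no eligibility limit. The loss is confined to the final tables and tests. A stopping count that differs from a table is not a contradiction.
- *Section 7.4 ends adverse-event collection in ineligible subjects.* Its exception concerns follow-up for survival, metastasis and relapse; it does not mention the window in 8.2.

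**Conclusion.** The point holds in a limited form. Read naturally, sections 12.2 and 12.3.2 together exclude from the final adverse-event comparison a group of treated subjects whom the protocol foresees and whose events it collects. This is a rule that works badly for safety, not a missing detail.

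A reader might infer that reported incidences will be too low. That follows only if ineligible subjects carry higher risk than eligible ones. At equal risk there is no bias, and at lower risk the error reverses. The documents give neither an ineligibility rate nor a risk by eligibility, so size and direction are unknown. The range of about 5 to 25 subjects per arm rests wholly on the assumed 2-10%.

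Monitoring during the trial, the sample size and the power for disease-free survival are not touched by this point. It should be corrected because the omission is avoidable and the data are already in hand, not because a large bias has been shown.

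**What to change.** Two sentences are enough.

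- In 12.2, limit the eligibility condition to the efficacy analyses.
- In 12.3.2, state that adverse events are tabulated and compared in all subjects who took at least one dose of TS-1 or UFT, whatever their eligibility, grouped by the drug taken.

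No change is needed to 8.1 or 8.2, which already cover any treated subject, or to the counts in 17.2.1, which are already unrestricted. No new data are required. The small cost is one additional analysis set, so denominators may differ between the safety and efficacy tables and should be labelled.

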12.4. Interim analysis

An interim analysis will be performed 1 year after completion of enrollment. The statistical significance of the inter-arm difference in overall survival will be studied, and an α consumption function will be used to make adjustments for the multiplicity of tests (the tests at the interim and final analysis) in order to maintain an α error of 5% for the study overall. An α consumption function of the O’Brien & Fleming type will be used.

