# Objective

To perform a randomized comparison of the efficacy of TS-1 adjuvant chemotherapy and a UFT control in patients with clinical and/or pathological Stage III or Stage IV A or B squamous cell cancers of the head and neck at sites other than the oropharynx who have undergone standard curative therapy consisting of surgical therapy and radiotherapy (including combination chemotherapy and radiotherapy) and are confirmed tumor-free. The primary endpoint is disease-free survival, and the secondary endpoints are relapse-free survival, overall survival, and adverse events.

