# Target sample size and study period

10.1. Target sample size

The target sample size is 500 subjects (250 in the TS-1 arm and 250 in the UFT arm).

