10.2. Study period

The enrollment and follow-up periods are as follows.

Enrollment period: 3 years (April 2006 to March 2009)

Follow-up period: 3 years after enrollment of the last subject (March 2012)

To study survival, all observations and tests are scheduled to be performed at one time 5 years after enrollment of the last subject (March 2014).

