# Statistical Considerations

12.1. Rationale for target sample size

The results of large-scale comparative studies in Western countries were used as the rationale for the disease-free survival rate in the control arm. This was done because there are no reports of Japanese studies in which UFT treatment was performed on control subjects as in the present study that could be evaluated.

The 3-year disease-free survival rate among subjects that had undergone curative therapy for Stage III, IVA, and IVB squamous cell cancers of the head and neck was approximately 35-45% in subjects that received radiotherapy postoperatively and approximately 40-59% in subjects that received combination radiotherapy and chemotherapy postoperatively.

From these results, it was hypothesized that the 3-year disease-free survival rate would be 50% in the control (UFT) arm. Thus, 216 subjects per arm would be required to have a hazard ratio of 0.7 (3-year disease-free survival rate: 61.6%) for the test (TS-1) arm versus the control arm with an enrollment period of 3 years, follow-up period of 3 years, two-sided α of 0.05, and statistical power of 80%. A sample size of 250 subjects per arm (500 in both arms) was selected because a power of test of at least 80% could be guaranteed with 250 subjects per arm.

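### Section 12.4 spends α on overall survival at the interim while disease-free survival is the primary endpoint, so the promised 5% for the whole study does not follow

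*Protocol*

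**What the plan says.** The Objective ranks the endpoints: "The primary endpoint is disease-free survival, and the secondary endpoints are relapse-free survival, overall survival, and adverse events". Section 12.1 sizes the trial on DFS alone: "it was hypothesized that the 3-year disease-free survival rate would be 50% in the control (UFT) arm", and "216 subjects per arm would be required to have a hazard ratio of 0.7 (3-year disease-free survival rate: 61.6"%), with "an enrollment period of 3 years, follow-up period of 3 years, two-sided α of 0.05, and statistical power of 80"%. It mentions no interim look. Section 10.1 then sets 250 per arm.

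Section 12.4 plans one interim analysis, 1 year after enrollment closes: "The statistical significance of the inter-arm difference in overall survival will be studied, and an α consumption function will be used". The spending function is of O'Brien-Fleming type, covers the interim and final tests, and is said to keep the α error of the whole study at 5%. The endpoint of the final test is not named.

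Section 17.2.1 lists as a ground for ending the study that "Interim analysis confirms the superiority of the test" treatment's efficacy, and a matching ground for inferiority. Neither names an endpoint.

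**The concern.** An α-spending function divides one error rate between successive looks at the same test statistic. The final critical value is derived from the correlation between looks, which for one statistic is the square root of the information fraction. Here the interim statistic is OS and the primary final statistic is DFS. Their correlation is not fixed by the OS information fraction, so the derived critical value does not deliver the stated 5%.

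Two things are at stake. First, the protocol asserts an error property that its own procedure does not secure. Second, it does not say whether the final DFS test is judged at the 0.05 used for sizing or at the reduced level left after the OS look. A stop for superiority could also be called on an endpoint the trial was not sized for, with no rule saying what that implies for DFS.

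**Working it through.** **1. Reproducing the sample size.** Inputs from section 12.1: control 3-year DFS 50%, HR 0.7, 3 years' accrual, 3 years' follow-up, two-sided 0.05, 80% power. With exponential DFS:

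- λ(UFT) = ln 2 / 3 = 0.2310 per year; λ(TS-1) = 0.7 × 0.2310 = 0.1617 per year. TS-1 3-year DFS = exp(−3 × 0.1617) = 61.6%, as stated.
- Events needed = 4 × (1.960 + 0.842)² / (ln 0.7)² = 247.
- Event probability with uniform accrual over A = 3 years and follow-up f after the last enrollment: p = 1 − [exp(−λf) − exp(−λ(f + A))] / (λA). At f = 3 this is 0.639 (UFT) and 0.512 (TS-1), mean 0.576.
- 247 / 0.576 = 429 in total, or 215 per arm against the stated 216. The sizing is sound.
- With 500 subjects: 288 events and power 85.7%, without an interim.

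**2. What the OS interim spends.** The protocol gives no OS rates. Assumption: control 3-year OS of 55 to 80% and OS HR 0.7. The interim then falls at 0.59 to 0.64 of the deaths expected at 3 years (for example 110 of 180 at 70% OS). With two-sided spending, α(t) = 2[1 − Φ(1.96/√t)]:

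- t = 0.60: interim 0.0114, final nominal level 0.0457.
- t = 0.65: interim 0.0151, final nominal level 0.0444.

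These final levels are right only if the final statistic has correlation √t with the interim one.

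**3. Study-wise error under the global null.** Let r be the correlation of interim OS with final DFS. Section 12.4 allows three readings:

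- A: final DFS is tested at the adjusted level.
- B: final DFS is tested at the full 0.05 used in sizing.
- C: spending covers OS at both looks, DFS is tested separately at 0.05, and either may claim superiority.

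| Reading | r = √t | r = 0.7 | r = 0.5 | Upper bound |
|---|---|---|---|---|
| A, t = 0.60 | 5.0% | 5.1% | 5.4% | 5.7% |
| A, t = 0.65 | 5.0% | 5.3% | 5.6% | 5.9% |
| B, t = 0.60 | 5.4% | 5.6% | 5.8% | 6.1% |
| B, t = 0.65 | 5.5% | 5.8% | 6.1% | 6.5% |

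The upper bound is the sum of the two levels; for B at t = 0.65 it is 0.0151 + 0.05 = 0.065. Reading C gives 7.1 to 9.1% for final OS–DFS correlations of 0.9 down to 0.5, with a bound of 10%.

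**4. Check with simulated patients.** Assumed death rates: 0.6 per year after relapse and 0.03 per year without. In this model the OS information fraction is about 0.52 and r about 0.58, against √0.52 = 0.72 for one statistic. In 12,000 null trials reading A gave 5.0 to 5.1%, B 5.1 to 5.3% and C 7.7 to 7.8%. The simulation standard error near 5% is √(0.05 × 0.95 / 12,000) = 0.2 points.

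**5. The DFS test alone.** DFS is tested once, with no earlier DFS look. Its own error is 4.4 to 4.6% in reading A (t = 0.60 to 0.65) and 5% in B and C.

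**6. The interim moved to DFS.** At f = 1 the event probabilities are 0.427 and 0.326, so DFS events = 250 × (0.427 + 0.326) ≈ 188. Information fraction = 188/288 = 0.65.

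| Convention | Interim level | Final level | Power, 250 per arm |
|---|---|---|---|
| Two-sided spending | 0.0154 | 0.044 | 85.0% |
| 0.025 per side | 0.011 | 0.047 | 85.3% |

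Both conventions total 5%.

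**The case against.** The strongest reply is that requiring survival evidence before an early stop is a defensible and conservative choice, and that no rule demands an interim look at the primary endpoint. This stands: monitoring OS is not itself an error. The fault is formal spending and stopping on OS with no stated link to the DFS test.

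It can also be said that the final DFS level, the testing order and the information fraction usually belong in a statistical analysis plan, which may exist. That is fair for the detail. But the protocol itself fixes OS as the interim endpoint and asserts the 5% property, so what it states needs correcting.

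Three stronger readings are tempting and not supported:

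- *That the type I error of the primary test is inflated.* It is not, because DFS is tested once.
- *That the OS interim pushes the study error to nearly 8%.* That figure arises only when a significant final OS result is also counted as a win. No section says so, and the Objective makes OS secondary. The same excess would exist with no interim at all.
- *That the 5-year date adds a further unadjusted OS test.* Section 10.2 says "To study survival, all observations and tests are scheduled to be performed at one time 5 years after enrollment of the last subject". In this protocol those words refer to clinical follow-up, and the sentence names no hypothesis test or level. It could equally be the date of the final OS analysis.

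**Conclusion.** The mismatch is real and lies in the text. The procedure in section 12.4 does not secure the study-wide 5% it claims, it leaves the final DFS level open between 0.05 and a reduced value, and the efficacy stops in section 17.2.1 name no endpoint.

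The numerical consequence is modest. With interim OS and final DFS as the only routes to a superiority claim, the excess is about 0 to 0.3 points under the assumed death rates, and up to about 1.5 points over other correlations and OS fractions of 0.60 to 0.65. It is about 2 to 4 points (7 to 9% in total) only if final OS is an independent superiority claim. All these figures rest on assumed OS rates or correlations, since the protocol gives none. The sample size is not at fault. This should be fixed, but it does not invalidate the primary test.

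**What to change.** Preferred change, before any interim data are seen:

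- In section 12.4, make DFS the endpoint of the interim test and of the α-spending. Define the information fraction as interim DFS events over planned final DFS events (about 188/288 = 0.65).
- State the spending convention, since the two sets of nominal levels in step 6 differ.
- In section 17.2.1, name DFS as the endpoint behind the superiority and inferiority stops.
- Give OS to the monitoring committee descriptively, and test it formally only after DFS is significant.

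Alternative: keep the OS interim, but state an explicit α split or hierarchy between OS and DFS and the level for the final DFS test. For example, at t = 0.60 a plain split would leave DFS 0.05 − 0.0114 = 0.0386, which holds 5% across the interim OS and final DFS tests whatever their correlation. Section 17.2.1 should then name OS.

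The preferred change costs wording in two sections and 0.4 to 0.7 points of power (85.0 to 85.3% against 85.7% with 250 per arm). No further patients or data are needed.
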